### Statistical analyses

We will calculate effect sizes using mean differences and standard deviations, and compare UCLA Loneliness Scale scores between the peer support group at 1 week after the session and the waitlist group at the end of the 2-week waiting period. Comparisons will be performed using the Wilcoxon rank-sum test. A t-test will also be conducted when the score distributions approximate normality. The analysis will include all participants with available outcome data for comparison. The same analyses will be applied to other measures.

In addition, we will explore a linear regression model with participants’ satisfaction as the outcome. Explanatory variables will include participant characteristics, peer supporter characteristics, and similarity between participants and peer supporters (e.g., age difference, shared topics of interest). Data from all participants who complete satisfaction assessments after peer support will be included. This exploratory model will be refined, guided by the statistical significance of variables and the Akaike information criterion. Based on the final model, we will propose a potential approach for matching participants with peer supporters.

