**Fig. 1 Fig1:**
[figure not shown]
Flow of participants through the study

Enrolled participants will access the registration page and enter demographic, clinical, and psychosocial information, and topics of interest selected from 18 predefined items (Supplementary Table 1). These items were developed based on the Zenganren × J-SUPPORT × SaQRA Research and Development Map [18].

Using Hibilog, an Interactive Web Response System (Accelight, Inc.), participants will be randomized using permuted block randomization to either the peer support group, which will immediately schedule a session, or the waitlist control group, which will schedule a session 2 weeks after registration. The block size will be confidential, with access limited to the system administrator. No stratification factors will be applied, given the small sample size in this pilot study. This randomized design with a waitlist group will enable us to simultaneously estimate intervention effects and examine satisfaction with the peer support session using data from both groups.

Participants will then attend peer support sessions and complete a suite of outcome measures described below. They may receive up to 4,000 Japanese yen (approximately 28 USD based on the exchange rate at the time of study planning) in Amazon gift cards based on completion of study questionnaires.

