### Measurements

Participants will complete web-based questionnaires via an electronic patient-reported outcome (ePRO) system at the following time points: registration, the end of the 2-week waiting period (for the waitlist group only), immediately after the peer support session, and 1 week after the session (Table 1). For the assessments at the end of the waiting period and 1 week after the peer support session, a 1-week window will be allowed, with automated reminders sent by the system if no response is recorded.

**Table 1 Tab1:** Measurement schedule

	Baseline	End of waiting period^a^^,b^	Immediately after peer support	1 week after peer support^b^
UCLA loneliness scale	●	●		●
Satisfaction			●	●
Usefulness			●	●
GAD-7	●	●		●
PHQ-9	●	●		●
CARS-J	●	●		●
SCNS-SF34-J	●	●		●
mDAMS	●	●	●	●
EORTC QLQ-C30	●	●		●

^a^Waitlist group only

^b^One-week window allowed

*GAD-7*, generalized anxiety disorder-7; *PHQ-9*, patient health questionnaire-9; *CARS-J*, concerns about recurrence scale Japanese version; *SCNS-SF34*, supportive care needs survey short form-34; *mDAMS*, modified version of the depression and anxiety mood scale; *EORTC QLQ-C30*, European Organization for Research and Treatment of Cancer quality of life questionnaire core 30

The primary outcome is the effect size of the intervention to reduce loneliness level measured using the UCLA Loneliness Scale 1 week after the peer support session. This 20-item questionnaire, each scored on a 1–4 point scale and a total score ranging from 20 to 80 points, assesses loneliness and has been validated in the Japanese population [21, 22].

Satisfaction with peer support will be used as an indicator for developing a matching algorithm. Items from the Japanese version of the Patient Satisfaction Questionnaire (PSQ-J) [23], which were originally used to assess satisfaction with medical care, are modified to assess satisfaction with peer support. The modified scale includes five items, each rated from 1 to 10 points, yielding a total score of 5–50 points.

To evaluate the usefulness of peer support, we developed an original ten-item measure consisting of nine items, each rated on a 7–point scale, and one open-ended comment for the session (Supplementary Table 3).

To measure anxiety over the past 2 weeks, the Generalized Anxiety Disorder-7 (GAD-7) will be used [24]. This consists of seven items plus one supplementary item, with total scores ranging from 0 to 21 points.

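### The UCLA effect size is the primary outcome, yet it is estimated from follow-up scores alone although a baseline score is collected in both arms; adjusting for it would add precision at no cost.

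*Protocol article*

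**What the plan says.** The Measurements section makes the effect size itself the primary outcome: "The primary outcome is the effect size of the intervention to reduce loneliness level measured using the UCLA Loneliness Scale 1 week after the peer" (the quote stops short; the time point is counted from the session). The Statistical analyses section gives the estimator: "We will calculate effect sizes using mean differences and standard deviations, and compare UCLA Loneliness Scale scores between the peer support group at 1 week". In that comparison the intervention arm is measured one week past its session and the control arm when its two-week wait ends. The section then gives the tests: "Comparisons will be performed using the Wilcoxon rank-sum test. A t-test will also be conducted when the score distributions approximate normality". The same analyses are to be applied to the other measures. The section mentions no baseline covariate and no change score.

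Baseline data exist. In Table 1 the row "UCLA loneliness scale" is marked at baseline as well as at both follow-up points. GAD-7, PHQ-9, CARS-J, SCNS-SF34, mDAMS and QLQ-C30 also have a baseline; only satisfaction and usefulness do not. The Procedure section puts this data entry before allocation: "Enrolled participants will access the registration page and enter demographic, clinical, and psychosocial information". Randomisation is described after that. On allocation it says: "No stratification factors will be applied, given the small sample size in this pilot study".

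**The concern.** With about 50 participants and no stratification, the arms can differ by chance in loneliness at entry. A comparison of follow-up scores alone carries that difference into the effect size in proportion to how strongly baseline predicts follow-up. In a trial whose stated aim is to supply an effect size for planning the next one, the precision of that figure is the main product. The article plans to collect the variable most likely to improve it and then leaves it out of the estimator.

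The consequence can be shown with the article's own planning figures. Suppose the true d is 0.30, the correlation is 0.5 and the arms differ by 0.3 SD at baseline. The unadjusted estimate is then centred on 0.15 or 0.45, depending on direction. Required size scales with 1/d², so the next trial would be put at about 470 × (0.30/0.15)² = 1,880 or 470 × (0.30/0.45)² ≈ 209 participants instead of 470.

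A smaller separate matter is that a t-test is added when the data look normal, with no criterion for normality and no statement of which result leads if the two tests disagree.

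**Working it through.** **Inputs from the article.** Planning d = 0.3, 90% power, two-sided 5%, 470 participants, pilot N = 50 (Sample size calculation). No stratification (Procedure).

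**Assumptions.** The allocation ratio is not stated; 1:1 is assumed, so 25 per arm with complete data. The correlation r between baseline and follow-up UCLA is not given; 0.3 to 0.8 is shown. The SD is taken as equal at baseline and follow-up.

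**Step 1: the article's own figure.** The exact noncentral-t calculation for d = 0.3, 90% power and two-sided 5% gives 234.46 per arm, so 235 per arm and 470 in total. The stated figure reproduces.

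**Step 2: precision as planned.** SE(d) ≈ √(2/25) = 0.283, and the 95% half-width is 1.96 × 0.283 = 0.554. Adding the small term for d itself gives SE = 0.284, so an observed d of 0.3 would have a CI of about −0.26 to 0.86.

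**Step 3: precision with ANCOVA on baseline.** SE ≈ √(2/25) × √(1 − r²) × √(47/46), where the last factor is the small-sample cost of estimating one slope. The equivalent unadjusted N is 50/(1 − r²), leaving that small factor aside.

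| r | SE | reduction in SE | 95% half-width | equivalent unadjusted N |
|---|---|---|---|---|
| none (as planned) | 0.283 | – | 0.554 | 50 |
| 0.3 | 0.273 | 4% | 0.535 | 55 |
| 0.5 | 0.248 | 12% | 0.485 | 67 |
| 0.7 | 0.204 | 28% | 0.400 | 98 |
| 0.8 | 0.172 | 39% | 0.336 | 139 |

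Simulation at 25 per arm (4,000 runs per value of r) gave ratios of adjusted to unadjusted SD of d of 0.96, 0.89, 0.73 and 0.62. The formula gives 0.96, 0.88, 0.72 and 0.61.

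**Step 4: chance imbalance.** The baseline mean difference has SD √(2/25) = 0.283 in SD units. It shifts the unadjusted d by r times the imbalance, so the shift has SD 0.283 × r.
- r = 0.5: SD 0.141; 0.3/0.141 = 2.12; two-sided probability of a shift above 0.3 SD about 3%.
- r = 0.8: SD 0.226; 0.3/0.226 = 1.33; probability about 18%.

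This shift is already contained in the SE of 0.283. It is not an additional error.

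**Step 5: the two tests.** With no true difference and 10,000 runs per distribution, taking Shapiro–Wilk in each arm as an assumed normality check, the Wilcoxon test alone rejected in 5.1% of runs. Counting either test as significant gave 6.0% with normal data and 5.5% with skewed data. The effect size and its SE are the same whichever test is run.

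**Step 6: value of r for the next trial.** If that trial also used ANCOVA, the normal-approximation size of 234 per arm multiplied by 1 − r² and rounded up would give 426, 352, 240 or 170 participants in total for r = 0.3, 0.5, 0.7 or 0.8. Reporting r therefore matters for planning.

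**The case against.** The strongest reply is that nothing here is invalid. Under randomisation the unadjusted estimate is unbiased and its interval is correct. The trial is an exploratory pilot, no decision in the article hangs on a p-value, and the Discussion concedes limited power and multiple testing. All of that stands, and it limits the point to efficiency.

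It may also be said that adjusted analyses belong in an analysis plan that is not shown. That stands in part: one cannot say that baseline is used nowhere, only that it is absent from the comparison described. But the article is not silent here. It names the estimator, the tests and the analysis set, so the point concerns a stated choice and not an omitted detail.

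A reader might infer more than the article supports in four ways:
- **That the effect size is far noisier than it need be.** This depends on r, which the article does not give. At r = 0.3 the gain is 4% of the SE; only from about 0.7 is it large. A high correlation is plausible for one scale repeated within weeks, but that remains an assumption.
- **That the conditional t-test adds to the noise.** It does not, because d comes from means and SDs regardless of the test. The Wilcoxon test is unconditional and the t-test is an addition, so the natural reading is that Wilcoxon leads.
- **That there is a 29% chance of an error as large as the planning effect.** That is the chance that the baseline imbalance itself exceeds 0.3 SD. The effect size moves by only r times that imbalance, hence about 3% to 18% for r from 0.5 to 0.8.
- **That adjustment would make the pilot estimate precise.** Even at r = 0.8 the half-width of 0.336 exceeds the planning d of 0.3.

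**Conclusion.** The point holds as a loss of efficiency. The stated primary comparison leaves out a prognostic measurement that is scheduled for both arms before allocation, in a trial whose primary outcome is the effect size. With 25 per arm, adjustment would be worth the equivalent of about 5 extra participants (r = 0.3) to 89 extra participants (r = 0.8). The result rests on the assumed 1:1 allocation, complete follow-up and an assumed correlation. The article analyses available data, so the numbers per arm may be lower and both half-widths wider.

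The two-test issue is minor: about one percentage point of type I error if either result is allowed to count, and no effect on the estimate. Severity: should be fixed, as a free improvement; the planned analysis is not wrong.

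**What to change.** 1. Make ANCOVA of follow-up UCLA on arm and baseline UCLA, in participants with outcome data, the single leading analysis.
2. Report the adjusted mean difference with its 95% CI, and that difference divided by an unadjusted SD, for example the pooled baseline SD. Dividing by the residual SD would inflate d and break comparability with the planning value of 0.3.
3. Treat every other measure that has a baseline in the same way.
4. Report the baseline to follow-up correlation of UCLA for sizing the next trial.
5. Keep the Wilcoxon test as a sensitivity analysis and drop the normality-conditional t-test.

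The cost is one paragraph of analysis wording, with no new data and no added burden on participants. It should be settled before outcome data are seen, since choosing to adjust afterwards would itself depend on the data.

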### Peer support

Participants randomized to the peer support group will schedule a session immediately after registration, while those in the waitlist group will schedule their session 2 weeks later. Reminders will be sent as needed by the study coordinating team if no reservation is made. Appointments will be made via a web system, allowing participants to select preferred dates and times from slots pre-specified by peer supporters. Participants in the waitlist group will be instructed not to engage in other peer support activities during the waiting period.

Each participant will receive a single approximately 40-min online session via Zoom, a web-based video conferencing system (Zoom Video Communications, Inc.). The session will be conducted by two peer supporters. Peer supporters will be provided with a manual that describes the procedures and general guidance, and the outline is shown in Supplementary Table 2. A primary supporter will lead the session, and a secondary supporter will manage time, record the session, and request questionnaire completion at the end. The second supporter will reduce the burden on the primary supporter by handling these tasks and will enhance session quality by addressing participants’ questions that the primary supporter may not be able to answer adequately. Peer supporters will report any issues occurring during each session, including technical problems (e.g., connectivity issues), adherence to session duration, and other difficulties encountered during the session.

Peer supporters will be recruited by CancerNet Japan, a non-profit organization that provides evidence-based cancer information and has offered a training program for breast cancer survivors to become peer supporters since 2007 [19]. Most graduates of this course engage in patient group activities or peer support, and CancerNet Japan maintains a nationwide network.

The eligibility criteria for peer supporters are: (1) female breast cancer survivors; (2) completion of the training program developed by the Ministry of Health, Labour and Welfare [3]; and (3) prior peer support experience. Criteria (2) and (3) are intended to ensure session quality. The training program is designed for individuals interested in peer support and focuses on sharing personal experiences with others [3]. It also provides guidance on protecting privacy and maintaining appropriate boundaries, such as refraining from offering opinions or advice regarding diagnoses or treatment.

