### Sample size calculation

One aim of this pilot study is to estimate the effect size required for a future randomized controlled trial, since no reference value is available in this study design. Therefore, we estimated the sample size assuming an effect size (Cohen’s d) of 0.3. A two-sample t-test with this effect size, 90% power, and a two-sided significance level of 5% requires 470 participants. Based on a previous study [32], we set the sample size at approximately 10% of that number, i.e., 50 participants.

In addition, a sample size of approximately 50 participants is considered sufficient for a multivariable linear regression model examining factors related to satisfaction with peer support. From this perspective as well, we concluded that 50 participants represent an appropriate sample size.

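### Peer support participants who never have a session have no scheduled follow-up loneliness score, so the available-data comparison describes attenders and is not fully protected by randomisation

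*Protocol article*

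**What the plan says.** Allocation comes before booking. In the Procedure section, "participants will be randomized using permuted block randomization to either the peer support group, which will immediately schedule a session"; the waitlist arm schedules its session 2 weeks after registration.

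The Measurements section lists the assessments after registration as "the end of the 2-week waiting period (for the waitlist group only), immediately after the peer support session, and 1 week after the session". UCLA appears in Table 1 at baseline, at the end of the wait and 1 week after the session, and the table's footnote a limits the end-of-wait column to the waitlist arm.

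The primary comparison in the Statistical analyses section is "between the peer support group at 1 week after the session and the waitlist group at the end of the 2-week waiting period". The analysis set is defined by one sentence: "The analysis will include all participants with available outcome data for comparison".

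For participants who do not book, the Peer support section says: "Reminders will be sent as needed by the study coordinating team if no reservation is made". The limitations in the Discussion do not mention non-attendance or the difference in how the two arms' outcomes are triggered.

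**The concern.** In the peer support arm a follow-up score can exist only if a session took place. In the waitlist arm it is requested from everyone, before any session, including people who would never have attended one. Attendance happens after randomisation, and here it filters one arm only. The planned contrast is therefore peer support attenders who respond against all waitlist responders.

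Two things are at stake. First, if attenders and non-attenders differ in loneliness, the two analysed groups differ for a reason unrelated to the session. Second, even without such a difference, the estimate is the effect among attenders, which is not the effect of being assigned to peer support. The article makes the effect size its primary outcome and wants it for planning a later trial, so the affected number is the pilot's main product.

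This is not a detail that an analysis plan can settle afterwards. A score that was never scheduled can be imputed but not recovered.

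**Working it through.** **1. The plan's own figure.** The Sample size calculation section states: "we estimated the sample size assuming an effect size (Cohen’s d) of 0.3" and "A two-sample t-test with this effect size, 90% power, and a two-sided significance level of 5% requires 470 participants". For a two-sample t-test with d = 0.3, 90% power and two-sided 5%, the normal approximation gives 234 per arm (468 in total). The exact noncentral t calculation gives 234.5, rounded up to 235 per arm, or 470. The figure reproduces. The pilot size is then fixed: "we set the sample size at approximately 10% of that number, i.e., 50 participants". The allocation ratio is not stated; I assume 1:1, so 25 per arm.

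**2. Who has a primary score, by arm.**

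| | Peer support | Waitlist |
|---|---|---|
| Would attend | Asked 1 week after the session | Asked at end of wait |
| Would not attend | Never asked | Asked at end of wait |

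**3. Selection term.** Let q be the share who never attend and g the difference in mean UCLA, in SD units, between non-attenders and attenders. Neither is in the article, so both are assumptions. Take no true effect, a within-group SD of 1, and a response from everyone who is asked.

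- Mean of peer support attenders: 0. Mean of the whole waitlist arm: q × g.
- Apparent d = −q × g / pooled SD.
- Waitlist variance: 1 + q(1 − q)g². The pooled variance is its average with 1.

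For q = 0.20 and g = 0.5, the waitlist variance is 1 + 0.2 × 0.8 × 0.25 = 1.04, the pooled SD is √1.02 = 1.01, and the shift is 0.10 / 1.01 = 0.099. A simulation of 20,000 trials with 25 per arm gave a mean d of −0.099.

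Absolute shift in d:

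| q | g = 0.25 | g = 0.5 | g = 1.0 |
|---|---|---|---|
| 4% (1 of 25) | 0.01 | 0.02 | 0.04 |
| 10% | 0.02 | 0.05 | 0.10 |
| 20% | 0.05 | 0.10 | 0.19 |
| 30% | 0.07 | 0.15 | 0.28 |

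If non-attenders are lonelier (g positive), the shift favours peer support. If they are less lonely (g negative), it goes the other way by the same amount. With g = 0 or q = 0 it is zero.

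**4. When would-be non-attenders on the waitlist also fail to respond.** If half of them do not answer and everyone else does, their share among waitlist responders is 0.10 / (0.80 + 0.10) = 0.11. The shift at g = 0.5 is 0.11 × 0.5 = 0.06. The table values are therefore upper bounds for each q and g.

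**5. Scale.** The standard error of d at 25 per arm is √(2/25 + 0.3²/(4 × 25)) = √0.0809 = 0.28.

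**6. Attender effect against as-randomised effect.** If non-attenders gain nothing, the as-randomised d is (1 − q) × 0.3. At the plan's power and significance level:

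| q | As-randomised d | Total N |
|---|---|---|
| 0% | 0.30 | 470 |
| 10% | 0.27 | 580 |
| 20% | 0.24 | 732 |
| 30% | 0.21 | 956 |

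This step needs no difference in loneliness between attenders and non-attenders.

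**The case against.** The strongest reply is that few people may fail to attend. Before randomisation, participants watch a video, give electronic consent, pass a telephone check, upload an identity document and complete baseline questionnaires. Eligibility requires daily use of digital devices and the ability to join online. They choose their own slot for one session of about 40 minutes, and the gift card depends on completing questionnaires. No booking deadline is stated, so a late booker still supplies a score. All of this stands: non-attendance may be small, and the article gives no rate.

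A reader might infer that non-attenders are lonelier, so that the plan builds in an apparent benefit and would undersize the next trial. The article does not support that. People with little need, or little time, may equally be the ones who do not book, and the bias would then run against peer support. A reader might also take the booking reminders as a sign that the sponsor expects non-booking. Reminders are routine and prove no such thing.

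It is also fair that this is an exploratory pilot whose sampling error is as large as or larger than the shift in every scenario tabulated, and that the later trial is to use a matched intervention and take the pilot's limitations into account. That lowers the urgency but does not remove the defect. A confidence interval shows sampling error; it does not show this bias, and the limitations do not list it.

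The choice of imputation method or sensitivity analyses can properly sit in an analysis plan, and their absence is not criticised here. The assessment schedule is different, because the article itself fixes it.

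**Conclusion.** The point holds as a defect of structure. The measurement schedule and the available-data rule together filter one arm on a post-randomisation event, so the primary comparison is not fully protected by randomisation and its effect size applies to attenders.

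A bias of known direction or size is not established. On the assumed middle case (20% non-attendance, 0.5 SD difference), d moves by up to about 0.10 either way, one third of the planning value of 0.3, and by about 0.06 if half of the would-be non-attenders on the waitlist do not respond. With full attendance, or attendance unrelated to loneliness, the shift is nil.

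The gap between the attender effect and the as-randomised effect rests on a separate assumption, that non-attenders gain nothing. At 20% non-attendance it is the difference between planning for 470 and for about 732, and it matters if the next trial has similar attendance and is analysed as randomised.

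**What to change.** - Keep the assessment 1 week after the session for attenders. Moving everyone to a single date counted from registration would redefine the primary outcome, and because slots vary, that date could fall before some sessions.
- Add a UCLA assessment at a pre-set time from registration for any peer support participant who has had no session by then, through the existing ePRO system. State in advance which score counts if a session follows later.
- Replace the analysis-set sentence with a statement that all randomised participants are analysed in their assigned arm.
- Report attendance and questionnaire response by arm.
- Give the attender-only estimate as a secondary result, labelled as such.

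The cost is one extra ePRO trigger, a protocol amendment, and somewhat more variable outcome timing in the peer support arm. The change is best made before follow-up is complete, because scores not requested at the time cannot be collected later.

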Nevertheless, several limitations should be noted. First, the intervention will include a single session, which may result in an insufficient effect size to achieve adequate statistical power. In addition, the effects of multiple sessions cannot be assessed in this trial. Future research may need to recruit a larger number of participants and examine the effectiveness of multiple sessions. Second, participants may receive informal support through social media or interactions at their medical institutions, which cannot be fully controlled or evaluated in this study. Third, although participants in the waitlist group will be instructed not to receive peer support outside the study during the waiting period, this protocol does not include procedures to monitor adherence to this instruction. In addition, psychosocial support outside the study will not be restricted due to ethical considerations. Therefore, monitoring and sensitivity analyses accounting for external exposure will be necessary in future studies. Fourth, while this protocol includes procedures to ensure and enhance the quality of peer support sessions, no quantitative scales to evaluate these aspects are included, which will need to be considered in future studies. Fifth, outcomes will be assessed 1 week after the session, and longer-term effects will remain unexplored. Sixth, given the many psychological measures collected, group differences may appear due to multiple testing. Thus, findings will need to be interpreted with caution. Finally, although this pilot study will provide insights into factors for matching, the small number of participants and peer supporters will limit the generalizability of these findings. Larger datasets will ultimately be required for model refinement. Taking these limitations into account, we will design subsequent confirmatory trials.

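### The satisfaction regression has no term for sessions that share a peer supporter, so if supporters recur, selection by significance and AIC is too favourable to supporter characteristics

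*Protocol article*

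**What the plan says.** In the protocol article, Statistical analyses, the second analysis is stated as "we will explore a linear regression model with participants’ satisfaction as the outcome". On covariates it says "Explanatory variables will include participant characteristics, peer supporter characteristics, and similarity between participants and peer supporters", with age difference and shared topics as the examples of similarity. On selection: "This exploratory model will be refined, guided by the statistical significance of variables and the Akaike information criterion". On use: "Based on the final model, we will propose a potential approach for matching participants with peer supporters". No supporter effect, cluster-robust variance or other allowance for dependence is named. The Sample size calculation section calls about 50 participants enough for this regression and counts only participants.

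The Peer support section describes how sessions arise. On number: "Each participant will receive a single approximately 40-min online session via Zoom". On staffing: "The session will be conducted by two peer supporters", with roles divided as follows: "A primary supporter will lead the session, and a secondary supporter will manage time, record the session, and request questionnaire completion at the end". Participants book from slots that supporters have offered. Supporters report their characteristics, experienced topics and PTGI-J once, at study start. The Discussion warns that "the small number of participants and peer supporters will limit the generalizability of these findings".

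**The concern.** Supporter characteristics are recorded once, so they are constant over all sessions of one supporter. If a supporter leads several sessions and some supporters are generally rated higher than others, ratings from the same supporter are correlated. The information on a supporter characteristic then comes mainly from the number of supporters, not from the number of sessions. A regression that treats sessions as independent gives standard errors that are too small for these variables. AIC computed from the same likelihood has the same fault.

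The selection rule carries this error forward. A characteristic that merely marks one well-liked supporter can be retained as if it predicted satisfaction in general, and can then enter the matching proposal, which is the second aim of the trial. The Discussion treats the small number of supporters as a limit on generalizability. It does not recognise that it also affects the validity of the tests used for selection.

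**Working it through.** **The plan's own figure.** For d = 0.3, two-sided 5% and 90% power, the normal approximation is n per arm = 2 × (1.960 + 1.282)² / 0.3² = 233.5, so 234 per arm and 468 in total. The exact t calculation gives 234.46, so 235 per arm and 470 in total, as stated. Ten percent is 47, set at 50. This figure concerns the between-group test and does not bear on the regression. For the regression no calculation is given.

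**Inputs from the article.** About 50 sessions, one per participant, with two supporters each. Avoiding all sharing would take 50 different primary supporters (100 different supporters if both roles count), against a number the article calls small.

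**Assumed inputs.** Number of primary supporters K = 5, 10, 20 or 25, with equal loads of m = 50/K sessions. ICC of satisfaction within primary supporter = 0.05, 0.10 or 0.20. The article gives none of these.

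**Formulas.** Design effect for a variable constant within supporter: DE = 1 + (m − 1) × ICC. Effective number of sessions: 50/DE. Approximate true size of a nominal 5% test: 2 × [1 − Φ(1.96/√DE)]. Example for K = 10, ICC 0.10: m = 5, DE = 1 + 4 × 0.10 = 1.4, effective number 50/1.4 = 35.7, size 2 × [1 − Φ(1.96/1.183)] = 9.8%.

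**Simulation.** Ordinary least squares with N = 50 and four covariates (a supporter characteristic, age difference, shared-topic count, a participant characteristic). All true coefficients are zero, with 4,000 runs per setting. The Monte Carlo standard error near 5% is √(0.05 × 0.95/4000) = 0.34 percentage points.

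True size of the nominal 5% test:

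| K | ICC | DE | Effective N | Supporter characteristic, formula | Supporter characteristic, simulated | Age difference, simulated | Shared topics, simulated |
|---|---|---|---|---|---|---|---|
| 5 | 0.05 | 1.45 | 34.5 | 10.4% | 9.1% | 5.2% | 6.1% |
| 5 | 0.10 | 1.90 | 26.3 | 15.5% | 13.9% | 5.5% | 7.6% |
| 5 | 0.20 | 2.80 | 17.9 | 24.1% | 22.2% | 6.9% | 10.6% |
| 10 | 0.05 | 1.20 | 41.7 | 7.4% | 7.8% | 5.0% | 5.7% |
| 10 | 0.10 | 1.40 | 35.7 | 9.8% | 9.0% | 5.5% | 5.6% |
| 10 | 0.20 | 1.80 | 27.8 | 14.4% | 12.6% | 6.4% | 7.5% |
| 20 | 0.05 to 0.20 | 1.075 to 1.30 | 46.5 to 38.5 | 5.9 to 8.6% | 5.7 to 8.1% | 5.2 to 5.6% | 5.1 to 6.8% |
| 25 | 0.05 to 0.20 | 1.05 to 1.20 | 47.6 to 41.7 | 5.6 to 7.4% | 5.8 to 6.9% | 4.4 to 5.2% | 5.0 to 5.9% |

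The participant characteristic stays near 5% throughout. With K = 50 (no sharing) or ICC = 0, all tests are near 5%.

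**AIC.** For one added variable, AIC improves when the likelihood-ratio statistic exceeds 2. Under independence, a null variable passes with probability 2 × [1 − Φ(√2)] = 15.7%. With DE = 1.4 this becomes 2 × [1 − Φ(√(2/1.4))] = 23.2%, and with DE = 1.9 it becomes 2 × [1 − Φ(√(2/1.9))] = 30.5%. So AIC gives no protection.

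**Why similarity variables suffer less.** They vary mostly between participants of the same supporter, so most of their information is within supporter. Shared topics are hit harder than age difference because a supporter who has experienced many topics shares more of them with everyone.

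**The case against.** The strongest reply is that the article is condensed and the model exploratory. It does not say that sessions are treated as independent, and a supporter effect could stand in the full protocol or analysis plan. It proposes only a potential matching approach, plans a confirmatory trial and says larger datasets will be needed. Data-driven selection already deprives the p-values of their nominal meaning. The number of supporters is unknown, and recruitment runs through an organisation with a nationwide network. With 20 to 25 supporters the inflation is modest.

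Much of this stands as a limit on size and certainty. It does not remove the point. The article names the model, the covariates and the selection rule, and those instructions, followed as written, use the wrong error term for supporter-level variables when supporters recur. Later data would refine a set of variables already filtered by that error.

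Three stronger readings are tempting, and the documents do not support them.

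- A reader might infer that p-values for all matching factors are too small. That is not shown: neither the number of supporters nor the ICC is given, and the two similarity measures named in the article stay close to nominal unless supporters are very few.
- A reader might infer that the UCLA comparison between arms is materially affected. Only about 25 sessions in one arm are involved. At ICC 0.10, K = 10 gives m = 2.5 and DE = 1.15, so the standard error of the difference rises by √((1 + 1.15)/2) − 1, about 4%. With K = 5, DE = 1.4 and the rise is √((1 + 1.4)/2) − 1, about 10%. That is minor for a pilot.
- A reader might want the pilot's ICC carried into the confirmatory sample size. A satisfaction ICC is not a loneliness ICC, and its approximate standard error with K = 10, m = 5 and ICC 0.10 is 0.13, larger than the value itself.

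**Conclusion.** The point holds conditionally and mainly for supporter characteristics. If primary supporters recur, which the article makes very probable, and the supporter ICC is positive, the stated regression and selection rule are too favourable to supporter-level variables. Allowing for simulation error and for the difference between formula and simulation, and for ICC 0.05 to 0.20, the true size of a nominal 5% test is about 8 to 14% with 10 supporters, 9 to 24% with 5, and 5 to 9% with 20 to 25. With 5 to 10 supporters, similarity variables reach about 5 to 7% (age difference) and 5 to 11% (shared topics). These figures rest on assumed supporter numbers, ICCs and equal loads, and on clustering by the primary supporter only. The effect could be negligible if supporters are many or alike.

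**What to change.** Fit the satisfaction model with a random intercept for the primary supporter and small-sample degrees of freedom, or with cluster-robust errors and a small-sample correction. Base selection of variables on that model. Report the number of sessions per primary and per secondary supporter, and the supporter ICC with its interval. If supporters turn out to be very few, present the effects of supporter characteristics as descriptive and do not let their p-values decide what enters the matching proposal.

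A random intercept for the primary supporter leaves any effect of the secondary supporter unmodelled, which is why sessions should be tabulated for both roles.

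The change is one of analysis wording. It needs no further participants or instruments, since the link between participant and supporter is already required to compute similarity. The price is wider intervals for supporter characteristics and an imprecise variance component when supporters are few.
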